## **8.5 Safety Analysis**

Analysis of safety endpoints will be assessed for all subjects receiving medication (Safety Population). Safety analysis will be undertaken on all study participants (safety population).

Adverse events will be coded using the Medical dictionary for regulatory activities (MedDRA) terminology. Prior to statistical analysis, all AEs will be checked for currency of terms using the most current version of MedDRA. The version of MedDRA used for final coding of the adverse events will be documented in the final study report. AE data will be listed individually and summarized by body system and preferred terms within a body system for each treatment group. Serious and/or unexpected AEs will also be discussed on a case-by-case basis. For the tabulation of AEs by body system, a subject will be counted only once in a given body system. For example, a subject reporting 'nausea and diarrhea' will be reported as one subject, but the symptoms will be listed as two separate AEs within the class. Therefore, the total number of AEs reported within a body system may exceed the number of subjects within the body system reporting AEs.

Each AE (based on preferred terminology) will be only counted once for a given subject. If the same AE occurred on multiple occasions, the highest severity will be assumed. Thus, subjects are not counted multiple times in a given numerator in the calculation of reaction rates for a specific AE.

Statistical comparisons will be made using Fisher's Exact test or Chi-Square test as appropriate.

Blood parameters (hematology and clinical chemistry) will be compared among groups using analysis of covariance using the screening value as the covariate. The dependent variable will be the post-baseline value; the factor of interest will be the treatment group (product) and value at screening (visit 1) will be the covariate.

## **8.6 Handling of Missing or Spurious Data**

In the case of outliers or spurious data, that is, data that is not plausible, a rule of plus or minus 3 standard deviations of the mean will be applied to determine if the value should be excluded from analysis. All missing data or data excluded from analysis will be detailed in the final report. Missing values for primary and secondary endpoints at visits 3, 4, 5 or 6 will be imputed with the more recent previously-available value (LOCF, or “last-observation-carried-forward” imputation). No imputation will be performed for any missing daily diary variables, taste and tolerability questionnaire values or missing values of parameters of safety.

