## **8.2 Sample Size**

For this study, twenty four (24) subjects per group are expected to complete the study. With an expected attrition rate of 20%, thirty (30) subjects per group are required for this study. A formal sample size was not done for this investigative study.

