## **8.4 Statistical Methods**

An effectiveness analysis based on the intent-to-treat population will be performed for all efficacy outcomes. Continuous variables will be presented as means with standard errors of the mean (SEM). Categorical variables will be shown as frequencies or proportions. Numerical efficacy endpoints will be

formally tested for significance by analysis of covariance. The dependent variable will be the post-baseline value; the factor of interest will be the treatment group (product) and value at baseline (usually visit 2, except for some laboratory tests [e.g. lipid profile] where baseline is visit 1) will be the covariate.

The ANCOVA approach differs from the simpler approach of comparing changes from baseline between products in that the ANCOVA adjusts for baseline in a more sophisticated way than simply subtracting it from the end of study value. The adjustment allows the ANCOVA to compensate for regression to the mean, floor effects, and other ways that the baseline value could influence change from baseline.

Where values being summarized as significantly non-normally distributed, as assessed by the Anderson-Darling test, a non-parametric test, such as the Wilcoxon or Mann-Whitney U test will be used.

A within-group analysis, if warranted, may be performed using a Student's paired samples t-test or Wilcoxon sign rank test.

All calculations and analyses will be performed using SAS version 9.2 or higher. For all statistical inferences, the tests will be performed at the two-sided, 0.05 level of significance.

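### Section 8.6 lets a 3 SD distance alone decide exclusion, so genuine values can be dropped from every endpoint and, if the data are skewed, the product comparison distorted

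*Protocol*

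**What the plan says.** Section 8.6 of the protocol opens with "In the case of outliers or spurious data, that is, data that is not plausible" and then says that "a rule of plus or minus 3 standard deviations of the mean will be applied to determine if the value should be excluded". It adds that "All missing data or data excluded from analysis will be detailed in the final report", and the later section on protocol deviations repeats the duty to document excluded data. The next rule in 8.6 concerns missing data: "Missing values for primary and secondary endpoints at visits 3, 4, 5 or 6 will be imputed with the more recent previously-available value".

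Section 8.4 specifies ANCOVA on the post-baseline value, with a rank-based test where the Anderson-Darling test shows significant non-normality, and "the tests will be performed at the two-sided, 0.05 level of significance". Section 8.2 says that "twenty four (24) subjects per group are expected to complete the study" and that "A formal sample size was not done for this investigative study".

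Section 8.6 does not define the reference mean and SD: pooled or per arm, raw value or change. It sets no assay or physiological limit, requires no source or laboratory check, and makes no exception for the primary endpoints in Section 6.1.

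**The concern.** The section treats an outlier and an implausible value as the same thing. An outlier is only far from the mean, and a correctly measured strong response can be one. Since 8.6 offers no other test, the distance decides, and a genuine outcome can be discarded because of its size. That makes the exclusion depend on the outcome after randomisation.

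The undefined reference SD matters because the two natural readings do different damage when data are right-skewed. With one pooled cut-off, the arm with the higher response loses more of its high values, so the difference shrinks. With a cut-off per arm, each arm loses its own tail. The difference is then nearly preserved, but the residual variance is understated and false positives rise. With about 48 completers, one or two deleted values can matter. Section 10.2 foresees a conclusion of either bioequivalence or superiority, and shrinkage towards zero would favour the first.

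**Working it through.** **The protocol's own figure.** From 24 completers and 20% attrition: 24 / (1 − 0.20) = 30 per group, as stated in Section 8.2. Section 8.6 gives no figure for the effect of the 3 SD rule, and no SD or effect size appears anywhere, so the distributions below are assumptions.

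**Can the rule act at this sample size?** The largest possible standardised distance in a sample of n is (n − 1)/√n:
- n = 24: 23/4.899 = 4.69
- n = 30: 29/5.477 = 5.29
- n = 48 (both arms pooled): 47/6.928 = 6.78

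All exceed 3, so it can.

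**How often, and with what effect?** The simulation used 20,000 trials per scenario, 24 per arm, one pass of the rule, unadjusted means and a two-sided 0.05 test. All simulated values are genuine, so every exclusion is an error. For log-normal data the log-scale SD is √ln(1 + CV²): 0.29, 0.47 and 0.63 for CVs of 30%, 50% and 70%.

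| Assumed data | Reference SD | Endpoint-visits losing at least one genuine value | Shrinkage of difference | Type I error |
|---|---|---|---|---|
| Normal | per arm | about 4% | about 0% | about 5% |
| Normal | pooled | about 8% | up to 1.6% | about 5% |
| Log-normal, CV 30/50/70%, ratio 1.3 | pooled | about 36%, rising to 75% | 6% / 13% / 19% | about 5% |
| Log-normal, CV 30/50/70%, ratio 1.3 | per arm | from about 22% | 0.6% / 2% / 4% | 6–8% |

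Type I error is taken with no true difference. Under normality the excluded values are about half high and half low. Under log-normality essentially all are high.

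Baseline adjustment changes little. With ANCOVA and a pooled SD the estimates went from 0.315 to 0.298, 0.336 to 0.298 and 0.365 to 0.304. The shrinkage is 1 − 0.298/0.315 = 5%, 1 − 0.298/0.336 = 11% and 1 − 0.304/0.365 = 17%.

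**Across endpoints.** Sections 6.1 and 6.2 give at least 12 endpoint-visits: red cell EPA and DHA at three times (6), four lipids (4), and serum phospholipid EPA and DHA if only these two are counted (2). If they were independent, the chance of at least one wrong exclusion would be:
- normal, per arm: 1 − 0.96^12 = 39%
- normal, pooled: 1 − 0.92^12 = 63%
- skewed, lowest case: 1 − 0.78^12 = 95%

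Repeated measures of the same fatty acids are correlated, so independence is a generous assumption.

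**Knock-on to imputation.** Table 1 in Section 3.3 schedules serum phospholipid samples at Visits 2 and 3 only. If an excluded Visit 3 value is then treated as missing, the only value to carry forward is baseline, and a strong responder would be scored as unchanged. Section 8.6 does not say that LOCF applies to excluded values, but does not rule it out.

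**The case against.** The strongest reply is that the rule is limited to data already judged implausible, so that 3 SD restrains discretion. The opening clause allows that reading. But it gives no criterion for implausibility and names outliers alongside spurious data, so the SD distance remains the only test that can be applied.

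Several other points stand in part:
- The rule is pre-specified and two-sided, exclusions must be reported, and Section 5.7 bars unblinding before database lock. This gives transparency, but a reported deletion is still a deletion.
- Section 8.4 offers a rank test, under which extreme values have little leverage. The order is not fixed, however. If exclusion comes first, it can hide the skewness that the Anderson-Darling test is meant to detect.
- The ratio of 1.3 is illustrative. The labelled EPA plus DHA content gives (325 + 225)/(300 + 200) = 1.10. At that ratio with a pooled SD the bias is at most 0.1 standard errors of the difference, and at 1.3 about 0.25. Confidence interval coverage at 1.3 with a pooled SD is about 93%, a modest departure.

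A reader might also infer a conflict with the intention-to-treat analysis. The text does not support that: Section 8.3.1 defines which participants are analysed, and dropping one value need not remove the participant.

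**Conclusion.** The defect is in a rule that the protocol itself fixes, not in a detail left to a later plan. Exclusion rests on distance alone, with no verified-error requirement and no defined reference mean or SD, for all endpoints including the primary ones. That much is certain from the text.

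The size of the harm is conditional. It is negligible if the data are near normal. If they are right-skewed, it is a loss of about 6–19% of the difference with a pooled SD, or about 0.6–4% with type I error of about 6–8% per arm. These figures rest on the assumed log-normal shape, CV of 30–70%, 24 per arm and, for shrinkage, a ratio of 1.3.

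It would be tempting to say that the rule does delete high responders, does bias the result, or is nearly certain to remove real data. The documents do not support this. They give no distribution, the rule also removes low values, and near-certainty over 12 endpoint-visits needs skewness. Larger losses (11–60%) appear if 5–10% of one arm are assumed to be extreme responders, but nothing in the protocol points to such a subgroup. The point deserves correction before analysis but does not by itself invalidate the trial.

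**What to change.** Amend Section 8.6 as follows:
- Use the 3 SD distance, with its reference mean and SD stated, only as a trigger for a blinded data query and re-check.
- Exclude a value only for a documented sampling, assay or transcription error, decided before unblinding.
- Keep all other values in the primary analysis.
- Report the analysis without flagged values as a sensitivity analysis.
- State whether LOCF applies to a value excluded for error.

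The cost is a few sentences and a small blinded data review. Intervals will be slightly wider when genuine extreme values are kept, which reflects the real variability.

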| Randomization                                                                                                                                                  |            |                     | X       |            |            |             |             |
| Blood Sample: Serum Phospholipid Fatty Acids                                                                                                                   |            |                     | X       | X          |            |             |             |
| Blood Sample: Total Red Blood Cell Fatty Acid Profile                                                                                                          |            |                     | X       |            | X          | X           | X           |
| Investigational Product Dispensed                                                                                                                              |            |                     | X       | X          | X          | X           |             |
| Investigational Product Returned                                                                                                                               |            |                     |         | X          | X          | X           | X           |
| Treatment Diary Dispensed                                                                                                                                      |            |                     | X       | X          | X          | X           |             |
| Treatment Diary Returned                                                                                                                                       |            |                     |         | X          | X          | X           | X           |
| Taste and Tolerability Questionnaire                                                                                                                           |            |                     |         | X          | X          | X           | X           |
| Review Adverse Events                                                                                                                                          |            |                     |         | X          | X          | X           | X           |

 Height will be measured at visit 1 only

 Urine pregnancy test is for women of childbearing potential only

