### **3.1.7 Early Termination/Discontinuation Visit**

Participants may withdraw voluntarily from participation in the study at any time. Subjects will be encouraged to visit the clinic for an early termination visit. At this visit, subjects will be encouraged to return study product and diaries, have blood pressure, heart rate and weight measured and provide a blood sample for analysis of safety parameters (hematology and clinical chemistry).

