## **8.3 Analytical Populations**

### **8.3.1 Intent-To-Treat Population**

Any subject known to start treatment (known to have taken  $\geq 1$  dose of study product) and completing at least one post-baseline visit will be included in the analysis of efficacy (intention-to-treat population).

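### LOCF that does not exclude baseline lets pre-treatment or part-way values stand as 24-week outcomes for fatty acids expected to rise on treatment

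*Protocol*

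**What the plan says.** Section 8.6 sets one rule for missing efficacy data: "Missing values for primary and secondary endpoints at visits 3, 4, 5 or 6 will be imputed with the more recent previously-available value". It does not limit the carried value to post-baseline measurements, and the protocol gives no second method or sensitivity analysis.

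The efficacy set in section 8.3.1 requires at least one dose and attendance after baseline; a participant "completing at least one post-baseline visit will be included in the analysis of efficacy".

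The sampling times are in Table 1 and section 3.2 (Diagnostic Tests):

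- The row "Blood Sample: Total Red Blood Cell Fatty Acid Profile" is marked at Visits 2, 4, 5 and 6 (Days 0, 84, 112 and 168).
- Serum phospholipid fatty acids are drawn at Visits 2 and 3 (Days 0 and 28).
- The lipid profile is drawn at Visits 1 and 6.

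Section 3.1.7 encourages withdrawing participants to attend a final visit and "provide a blood sample for analysis of safety parameters (hematology and clinical chemistry". No fatty acid sample is listed there, and the hematology and chemistry panel in section 7.4 contains no lipids.

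Section 8.2 says that "twenty four (24) subjects per group are expected to complete the study" and "With an expected attrition rate of 20%, thirty (30) subjects per group are required for this study". It gives no effect size or standard deviation: "A formal sample size was not done for this investigative study".

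**The concern.** LOCF assumes that a participant's value would have stayed where it was last seen. Sections 1.3.2 and 2.1 set out to measure EPA and DHA in red cells after six months of supplementation, so the outcome is expected to move over exactly the interval that the rule treats as flat.

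The sampling schedule makes this worse. RBC fatty acids have no sample between Day 0 and Day 84, so a leaver in that gap who attended Visit 3 is analysed with a value taken before the first dose. For serum there is one post-baseline sample, and for lipids one, so any missing value there can only be replaced by a pre-treatment one.

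Two things are at stake. If dropout is equal in amount and timing, the filled values pull the arms together, add variance and cost power. If it is unequal, for example through taste or tolerability, the arm that loses more participants looks less effective even when the products are identical. The filled values also enter the ANCOVA as if they had been observed.

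**Working it through.** **1. The plan's own figure.** 24 / (1 − 0.20) = 30 per group, 60 in total. This reproduces section 8.2. Attrition is 30 × 0.20 = 6 per arm over the whole 168 days.

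**2. Which value is carried for the 24-week RBC outcome.** Assume that dropout is uniform over 168 days (the protocol gives no timing).

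| Leaves between | Expected number per arm | Value used at 24 weeks |
|---|---|---|
| Day 0 and Day 28 | 6 × 28/168 = 1 | none; normally outside the efficacy set |
| Day 28 and Day 84 | 6 × 56/168 = 2 | baseline |
| Day 84 and Day 112 | 6 × 28/168 = 1 | week 12 |
| Day 112 and Day 168 | 6 × 56/168 = 2 | week 16 |

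The efficacy set is 30 − 1 = 29. Imputed: (2 + 1 + 2)/29 = 5/29 = 17%. Baseline carried: 2/29 = 7%. If every dropout fell between Visits 3 and 4, both shares would be 6/30 = 20%.

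For 1-month serum, early leavers are outside the set and later leavers have the value, so dropout leads to almost no imputation. Only a missed Visit 3 or a lost sample is filled, always with baseline. If an early termination visit before Day 28 counts as the post-baseline visit, which section 8.3.1 leaves open, those participants enter with baseline for both primary endpoints.

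**3. Dilution of the mean rise.** Let D be the mean 24-week rise, with 70% of it reached by week 12 and 85% by week 16 (assumptions). Loss = (2 × 1 + 1 × 0.30 + 2 × 0.15)/29 = 2.6/29 = 9% of D. With 50–90% reached by week 12 and 67–95% by week 16, the loss is 8–11%. The worst case is 20%.

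**4. False difference under unequal dropout, no true difference.** Take 3 against 9 dropouts (10% against 30%), uniform timing, same response curve.

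- Arm losing 3: 0.5 outside the set, 1 baseline, 0.5 week 12, 1 week 16. Loss = (1 + 0.15 + 0.15)/29.5 = 0.044 D.
- Arm losing 9: 1.5 outside, 3 baseline, 1.5 week 12, 3 week 16. Loss = (3 + 0.45 + 0.45)/28.5 = 0.137 D.
- Difference: about 0.09 D, or 0.10 D in round terms. If all carry baseline: (9 − 3)/30 = 0.20 D.

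For scale, the products provide 325 + 225 = 550 mg and 300 + 200 = 500 mg EPA+DHA per capsule, a 10% difference. If response were proportional to dose (an assumption), the true difference would itself be about 0.10 D.

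**5. Power and type I error.** Simulated ANCOVA, 30 per arm, two-sided 0.05 as in section 8.4. Assumed: baseline SD 0.25 D, baseline slope 0.7, residual SD 0.3 D, dropout unrelated to outcome, response curve as in step 3.

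| Case | Observed values only | LOCF, uniform timing | LOCF, all carry baseline |
|---|---|---|---|
| Power, true difference 0.25 D, 20%/20% dropout | about 79% | 52–54% | 31% |
| Type I error, 15%/25% | about 5% | 7% | 12–13% |
| Type I error, 10%/30% | about 5% | 14–17% | about 36% |

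The ranges come from repeated runs. These rows treat dropout as random within each arm. Fixing the counts lowers type I error: exactly 3 against 9 with all baseline carried gives 26%. Exactly 4 against 8 gives about 5% (all baseline) or 6.5% (uniform timing). In the all-baseline 4-against-8 case the false difference is still (8 − 4)/30 = 0.13 D; it is masked by the added variance.

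**The case against.** The strongest reply is that the damage is easily overstated. A reader might infer that about a fifth of the primary data would be set to no effect and that any dropout imbalance produces a false product difference. The documents do not support either. The 20% is attrition over the whole study. Those lost before Visit 3 normally fall outside the efficacy set, and those lost after Visit 4 carry a value obtained after half or two-thirds of the treatment period, which is a partial response. The 1-month serum endpoint is barely touched by dropout. A modest imbalance (15% against 25%, uniform timing) gives a false difference of about 0.04 D and type I error near 7%, and late dropout does less still. All of this stands, and it sets the size of the point.

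A second reply is that balanced LOCF is conservative. It is for a claim of difference. Section 10.2, however, would count bioequivalence as well as superiority as efficacy, and a rule that pulls the arms together favours a finding of similarity.

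A third is that the remedy has limits. A leaver before Visit 4 has no post-baseline RBC value, so a repeated-measures model gains almost nothing from that participant. Both that model and observed-value ANCOVA assume data missing at random, which withdrawal for tolerability may strain. An early-termination sample is not a 24-week value, and that visit is only encouraged. This stands too, and is why the fix includes a sensitivity analysis.

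Finally, section 8.2 describes the study as investigative, without a formal sample size. That lowers the grade but does not justify the rule. Nor can an analysis plan that is not shown be presumed to cure it, since the protocol itself fixes the method.

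**Conclusion.** The concern holds in a limited form. Section 8.6, read with the sampling schedule and section 8.3.1, allows a pre-treatment RBC value to be analysed as the 24-week primary outcome and substitutes part-way values for later leavers. It always replaces a missing serum value with baseline and a missing end-of-study lipid value with screening.

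Up to 20% of 24-week RBC values would be imputed. Under uniform dropout the figures are about 17% imputed and about 7% at baseline. The likely cost is a material loss of power when dropout is balanced, and a modest inflation of type I error only when dropout is markedly unequal. The 31% power and 36% type I error figures describe a worst case in which every dropout carries baseline.

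The mechanism follows directly from the text. The magnitudes rest on an assumed rise, SD, response curve, dropout timing and dropout imbalance, none of which the protocol gives. This should be fixed; it does not invalidate the design.

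**What to change.** - In section 8.6, delete LOCF for the primary and secondary efficacy endpoints.
- In section 8.4, analyse RBC EPA and DHA at weeks 12, 16 and 24 in a mixed model for repeated measures, with product-by-visit and baseline-by-visit terms and the week-24 product contrast as primary. ANCOVA on observed week-24 values is an acceptable simpler choice.
- Analyse Visit 3 serum phospholipids and Visit 6 lipids by ANCOVA on observed values.
- Add a sensitivity analysis for data not missing at random, such as a tipping-point analysis.
- Optionally, in section 3.1.7, add a fatty acid tube to the blood draw already listed at early termination, and analyse the result at its actual study day rather than as a 24-week value.

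The cost is slightly more programming and a somewhat smaller analysed number (about 24 per arm at week 24 if attrition is as planned). If the tube is added, each withdrawn participant who attends gives about 5 mL more blood for one more assay.
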